## Methods

### Study Design

This fully remote, single-arm, National Institutes of Health (NIH) Stage II decentralized behavioral trial delivering a multicomponent, personalized BCT intervention will enroll 100 caregivers of persons living with ADRD into a 12-week trial comprised of a 2-week baseline period and a 10-week intervention period [58]. The single-arm design of this trial was used to minimize sample size requirements and ensure all eligible caregivers were able to participate in the intervention. Participants will be provided with a Fitbit device for continuous activity tracking and electronic surveys delivered to their smartphones. Fitbit data will be retrieved directly via an Application Programming Interface call. All survey data will be collected and managed using REDCap (Research Electronic Data Capture), a secure, web-based software platform designed to support data capture [59,60]. An overview of the 12-week trial timeline can be seen in Figure 1.

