### Baseline Period

On the participant’s assigned start date, they will begin a 2-week baseline period to assess adherence to the study protocol and preintervention behavioral automaticity. Participants will not receive any BCTs during the baseline period. Instead, they will engage in their usual level of activity, wear the Fitbit device continuously, and complete weekly SMS text message–delivered surveys via REDCap (delivered using the Automated Survey Invitations application) consisting of the 4-item Self-Report Behavioral Automaticity Index (SRBAI) [76] to assess the MoBC and a single-item assessing overall health from the EuroQol EQ-5D-5L.

To be eligible to continue into the 10-week intervention period, participants must wear their Fitbit for at least 10 hours each day for at least 12 of the 14-day baseline period and must complete one of the 2 weekly surveys. We have successfully achieved desired samples without more-than-expected baseline attrition using similar adherence thresholds used in other remotely delivered behavioral trials [77-80]. Participants who do not meet adherence requirements for the 2-week baseline period will be removed from the study. Figure 3 outlines a timeline of baseline, intervention, and postintervention digital surveys and activities for participants eligible after baseline.

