### Primary Outcome and Analysis

The primary outcome is a binary indicator of habit formation. The goal is to identify whether a significant proportion of caregivers (≥50%) develop habitual hourly walking, thereby disrupting the time they spend sedentary. A participant will have successfully formed a habit of walking if they attain walking 250 steps each hour during their preidentified, preferred 4-hour period each day for 7 consecutive days during the 70-day intervention period (Figure 6). We used this definition of habit to reflect behavioral consistency in physical activity performance. Consistency of physical activity behavior has been found to be a strong correlate of habit in previous research [84]. To ensure that our definition of habit does not bias results, we will conduct sensitivity analyses using 10-day, 14-day, and 21-day periods in addition to the 7-day period used for our primary outcome. We will use a null hypothesis rate of 30% and will compare the achieved proportion of habit formation versus this null level, using a 1-sample binomial test with a 2-sided α at 5%. The rate of habit formation will be summarized using the observed proportion along with a 95% CI. We will also use Kaplan-Meier curves to identify estimates of the time-to-event for habit formation in the sample.

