A final secondary outcome for the trial is examining HTEs for habit formation and on changes in behavioral automaticity by conducting analyses of HTEs across participants. This will involve examining the heterogeneity in time to attaining the first operationalization of habitual hourly walking due to the BCT intervention.

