### Exploratory Outcomes

Exploratory analyses will be conducted to examine the important potential moderating variables that may influence the effect of the intervention on habitual hourly walking. These include caregiver sociodemographic characteristics from a survey required by the funder (eg, sex at birth, gender identity, sexual orientation, race, ethnicity, highest education level, household income level, occupation category, current marital status, living situation, insurance status, and zip code) and self-reported details of caregiving (eg, number of care recipients, relation to person with ADRD, primary caregiver status, length of time providing care, hour providing care per week, living situation, time since diagnosis, and demographic characteristics of person with ADRD). Participants will complete pre- and postintervention measures to assess various components of caregiver well-being, including (1) burden using the Zarit Burden Interview Short Form (12 items), which uses a rating scale of 0 (never) to 4 (nearly always) with a higher total score equating to higher burden [64], (2) stress using the PSS-10 validated in English and Spanish with a rating scale of 0 (Never) to 4 (Very Often) with a higher total score equating to higher stress [65,66]; (3) anxiety symptoms using the STAI-S with 2 scales, the State anxiety and Trait anxiety scale, both with a scale of 0 (not at all) to 3 (very much so) with a higher total score equating to higher anxiety symptoms [67]; (4) depressive symptoms using the adapted PHQ-9; excluding the final question assessing thoughts of suicide or harming oneself) with a 4-point Likert scale from 0 (not at all) to 3 (nearly every day) with a higher total score equating to higher depressive symptoms [68]; and (5) quality of life using the EuroQol-EQ-5D-5L with a level score of 1 (indicating no problem) to 5 (indicating unable to or extreme problems) for 5 health state items and a 0 (worst health you can imagine) to 100 (best health you can imagine) visual rating scale for overall current health converted into an index value [69]. The EuroQol-EQ-5D-5L official Spanish translation was obtained from the EuroQol Research Foundation, which follows a standardized translation protocol that involves a forward and backward translation process [70,71]. Additionally, participants will complete preintervention measures of the NPIQ, a brief informant-report of symptom severity and associated caregiver distress for 12 neuropsychiatric domains, and the Katz ADLs, a binary checklist assessing the functional independence or dependence of older adults in performing 6 basic ADLs [72-75].

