
### Sample Size Calculation

A sample of 100 participants is planned for enrollment into this remote trial. Up to 20% attrition is expected following the 2-week baseline period due to failure to meet wearable device and survey adherence requirements (n=20). An additional 25% attrition is expected after the 10-week intervention period due to participants becoming lost to follow-up, withdrawing, or other (n=20). The expected attrition throughout the intervention period is estimated as such because of the burdens caregivers experience due to the nature of their unique responsibilities, not limited to time constraints and motivation, which may produce barriers to longitudinal research participation [87]. We have attempted to design this trial to minimize barriers to participation for caregivers specifically, yet have estimated attrition similar to that in other longitudinal physical activity trials with caregivers to be conservative [88,89].

The trial still will have a sufficient sample (n=60) to provide adequate power. Assuming a null habit formation rate of 30% with a sample size of n=60, a 1-sided, one-sample binomial test at 5% significance will have about 92% power to declare the BCT intervention effective if the true habit formation rate is at 50% or above. We believe the null hypothesis for habit formation is conservative, as caregivers spend 80% of their time being sedentary.

To anticipate the variability due to the proposed total sample size of 60, we calculated the power to detect a difference between 20% habit formation (in the group of participants without increased behavioral automaticity) versus 60% habit formation (in the group of participants with increased behavioral automaticity) under different scenarios. Specifically, when 30% of the participants experience an increase in behavioral automaticity, there is 86% power to detect the difference. When 50% of the participants experience increases in behavioral automaticity, the power increases to about 89%.

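### In a single arm, spread in time to habit is not treatment-effect heterogeneity and its correlates are not effect moderators; the 30% null also lacks a quantitative basis, and no stated analysis uses the baseline step counts

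*Protocol article*

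**What the plan says.** **Design.** Under Study Design, "The single-arm design of this trial was used to minimize sample size requirements". Everyone who passes the baseline period and the comprehension survey gets the text messages.

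**Outcome.** Primary Outcome and Analysis defines habit as meeting the hourly step target in the chosen 4-hour block on 7 consecutive days within the 70 intervention days. The observed proportion is tested against 30%.

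**Heterogeneity and moderation.** Secondary Outcomes and Analysis plans heterogeneity of treatment effects for habit formation and for change in automaticity, described as "examining the heterogeneity in time to attaining the first operationalization of habitual hourly walking due to the BCT intervention". Exploratory Outcomes plans to "examine the important potential moderating variables that may influence the effect of the intervention on habitual hourly walking".

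**Support for the null.** Sample Size Calculation gives one sentence: "We believe the null hypothesis for habit formation is conservative, as caregivers spend 80% of their time being sedentary".

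**Baseline.** Participants wear the Fitbit for two weeks at usual activity without any messages. The stated purpose is that "they will begin a 2-week baseline period to assess adherence to the study protocol and preintervention behavioral automaticity". Wear time decides who continues. The general statistical section promises descriptive summaries of baseline measurements, and Potential Limitations says daily steps are measured over the whole trial. No primary, secondary or exploratory analysis is said to use baseline step counts.

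**The concern.** A treatment effect compares an outcome with what it would have been without treatment. Here the outcome exists only under treatment and each person has one time to habit. That time mixes usual walking in the chosen hours, chance and any effect. A covariate related to it may simply mark people who already walked more. The Methods definition sharpens this: it counts 250 steps per hour in absolute terms, while the Abstract and the messages speak of additional or extra steps, so someone who already reaches 250 in the chosen block can count as a success without changing.

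The primary test leans on the same missing information. With no control group, the 30% null stands in for the untreated rate. If it is too low, ordinary walking is credited to the intervention; if it is too high, a real effect may be missed.

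At stake are reports of differential effect that are really prognosis and chance, and a claim of effectiveness resting on an undocumented reference value.

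**Working it through.** **1. The plan's own power figure.** Inputs from Sample Size Calculation: n = 60, null 0.30, true rate 0.50, 1-sided 5%, exact binomial.

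- P(X ≥ 24 | 0.30) = 0.0632 and P(X ≥ 25 | 0.30) = 0.0362, so the rule is at least 25 of 60.
- Power = P(X ≥ 25 | 0.50) = 0.9225. The stated figure of about 92% is reproduced.
- Primary Outcome and Analysis states a 2-sided test at 5%. The exact 2-sided p-value is 0.0657 at 25 and 0.0335 at 26, so that rule is at least 26 of 60, with power 0.877. The two sections need reconciling; both rules are carried below.

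**2. Sensitivity to the null.** Suppose the intervention does nothing and the true untreated habit rate is p. The chance of declaring success is P(X ≥ r | n = 60, p). The values of p are assumptions; the article gives no untreated rate.

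| Untreated rate p | r = 25 (1-sided rule) | r = 26 (2-sided test) |
|---|---|---|
| 20% | 0.000 | 0.000 |
| 30% | 0.036 | 0.020 |
| 35% | 0.171 | 0.113 |
| 40% | 0.444 | 0.344 |
| 45% | 0.741 | 0.650 |

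**3. Does 80% sedentary time give 30%?** No. The null is the share of people with at least one run of 7 successful days in 70. It depends on the daily chance of meeting the target in four particular hours, on how that chance varies between people, and on dependence between days. A share of time spent sedentary fixes none of these.

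**4. Can the baseline inform the null?** Yes, but not through the raw 14-day habit rate. A 14-day window has 14 − 7 + 1 = 8 possible 7-day runs; 70 days have 70 − 7 + 1 = 64. Assume identical people and independent days with daily success probability q, and track the current run length day by day:

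- A 70-day habit rate of 0.30 corresponds to q = 0.526. At that q, the 14-day rate is only 0.048.
- With between-person variation (assumed beta distribution for q, precision 10, 4 or 2), the same 0.30 corresponds to mean daily attainment of 0.48, 0.44 or 0.40.

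So the same null corresponds to a mean daily attainment between 0.40 and 0.53, depending on assumptions. Baseline daily attainment can be translated into a 70-day rate only with those assumptions stated.

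**5. Heterogeneity and moderation.** No arithmetic is needed. One arm, one time to habit per person and an outcome defined only under treatment leave no contrast that could vary between people. Automaticity is measured at baseline, so its change can be computed, but change without a control is not effect.

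**The case against.** Several counter-arguments have weight.

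- **Much may be left to the analysis plan.** The article names no heterogeneity model, and a separate plan is to be posted. That covers model details. It does not cover the stated target: no model can recover an effect contrast for time to habit from treated observations alone.
- **The baseline data are not idle.** A reader might infer that the Fitbit baseline is wholly unused. The article does not support that: wear time gates entry, and descriptive use is allowed for. What stands is that no stated analysis uses the baseline step counts.
- **The null is not without rationale.** A very sedentary group should have a low untreated rate, so the sentence points in a sensible direction. It still does not derive 30%. A reader might also infer that 30% is too low; nothing in the article shows this, and the true untreated rate could be well below it.
- **Constant attainment is not evidence of no effect.** If everyone had an unchanging 58.6% daily chance and days were independent, half would form a habit within 70 days. One might read this as success without effect, or take the distance from 52.6% as the size of effect being tested. Neither is supported. A steady 58.6% during the intervention is equally compatible with a large effect from day 1; no figure in the article gives such a daily rate; and the distance changes with between-person variation.
- **The consequence is limited.** Heterogeneity is secondary and moderation exploratory, so mislabelling them does not touch the primary test. The null does.

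**Conclusion.** The point holds in three bounded parts.

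1. The time-to-habit heterogeneity and moderator analyses are misnamed: they describe predictors of outcome. This follows from the design and needs no numerical assumption. The causal limit extends to heterogeneity in automaticity change.
2. The 30% null is supported only qualitatively. The power arithmetic is sound, but at an untreated rate of 40% a no-effect trial of 60 succeeds 44% of the time (1-sided rule) or 34% (2-sided test). The 40% is illustrative; the range of 20% to 45% takes the 1-sided figure from essentially zero to 74%.
3. The baseline step counts, which bear on both problems, appear in no stated analysis.

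The baseline does not turn this into a controlled comparison. A reader might expect a within-person model to deliver true treatment-effect heterogeneity. It delivers heterogeneity of change, which also contains time trend, reactivity to a new device and regression to the mean in people recruited for low activity.

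**What to change.** - Relabel the time-to-habit heterogeneity and moderator analyses as analyses of predictors of habit formation, and those of automaticity change as predictors of change.
- Add a within-person model of daily steps, or daily target attainment, in the chosen 4 clock hours over baseline and intervention days: fixed period effect, random intercept, random period slope, and period-by-covariate terms. Report the slope variance and interactions as heterogeneity and predictors of within-person change, not of treatment effect.
- Report baseline daily attainment in those hours beside the 30% null, with the 70-day run rate it implies under stated assumptions on between-person variation and day-to-day dependence. Do not use the raw 14-day habit rate.
- Justify the 30%, and show how the primary conclusion changes over a range of nulls.

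**Cost.** Analysis work only; the steps are already being collected, and analysis is scheduled for Fall 2026, so this can still be prespecified. The downside is interpretive: the block is chosen after baseline, and before-after change must be labelled as uncontrolled, with trend, device reactivity and regression to the mean named.

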### Exploratory Outcomes

Exploratory analyses will be conducted to examine the important potential moderating variables that may influence the effect of the intervention on habitual hourly walking. These include caregiver sociodemographic characteristics from a survey required by the funder (eg, sex at birth, gender identity, sexual orientation, race, ethnicity, highest education level, household income level, occupation category, current marital status, living situation, insurance status, and zip code) and self-reported details of caregiving (eg, number of care recipients, relation to person with ADRD, primary caregiver status, length of time providing care, hour providing care per week, living situation, time since diagnosis, and demographic characteristics of person with ADRD). Participants will complete pre- and postintervention measures to assess various components of caregiver well-being, including (1) burden using the Zarit Burden Interview Short Form (12 items), which uses a rating scale of 0 (never) to 4 (nearly always) with a higher total score equating to higher burden [64], (2) stress using the PSS-10 validated in English and Spanish with a rating scale of 0 (Never) to 4 (Very Often) with a higher total score equating to higher stress [65,66]; (3) anxiety symptoms using the STAI-S with 2 scales, the State anxiety and Trait anxiety scale, both with a scale of 0 (not at all) to 3 (very much so) with a higher total score equating to higher anxiety symptoms [67]; (4) depressive symptoms using the adapted PHQ-9; excluding the final question assessing thoughts of suicide or harming oneself) with a 4-point Likert scale from 0 (not at all) to 3 (nearly every day) with a higher total score equating to higher depressive symptoms [68]; and (5) quality of life using the EuroQol-EQ-5D-5L with a level score of 1 (indicating no problem) to 5 (indicating unable to or extreme problems) for 5 health state items and a 0 (worst health you can imagine) to 100 (best health you can imagine) visual rating scale for overall current health converted into an index value [69]. The EuroQol-EQ-5D-5L official Spanish translation was obtained from the EuroQol Research Foundation, which follows a standardized translation protocol that involves a forward and backward translation process [70,71]. Additionally, participants will complete preintervention measures of the NPIQ, a brief informant-report of symptom severity and associated caregiver distress for 12 neuropsychiatric domains, and the Katz ADLs, a binary checklist assessing the functional independence or dependence of older adults in performing 6 basic ADLs [72-75].

### Sample Size Calculation

A sample of 100 participants is planned for enrollment into this remote trial. Up to 20% attrition is expected following the 2-week baseline period due to failure to meet wearable device and survey adherence requirements (n=20). An additional 25% attrition is expected after the 10-week intervention period due to participants becoming lost to follow-up, withdrawing, or other (n=20). The expected attrition throughout the intervention period is estimated as such because of the burdens caregivers experience due to the nature of their unique responsibilities, not limited to time constraints and motivation, which may produce barriers to longitudinal research participation [87]. We have attempted to design this trial to minimize barriers to participation for caregivers specifically, yet have estimated attrition similar to that in other longitudinal physical activity trials with caregivers to be conservative [88,89].

The trial still will have a sufficient sample (n=60) to provide adequate power. Assuming a null habit formation rate of 30% with a sample size of n=60, a 1-sided, one-sample binomial test at 5% significance will have about 92% power to declare the BCT intervention effective if the true habit formation rate is at 50% or above. We believe the null hypothesis for habit formation is conservative, as caregivers spend 80% of their time being sedentary.

To anticipate the variability due to the proposed total sample size of 60, we calculated the power to detect a difference between 20% habit formation (in the group of participants without increased behavioral automaticity) versus 60% habit formation (in the group of participants with increased behavioral automaticity) under different scenarios. Specifically, when 30% of the participants experience an increase in behavioral automaticity, there is 86% power to detect the difference. When 50% of the participants experience increases in behavioral automaticity, the power increases to about 89%.

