### General Statistical Analytical Approach

Baseline measurements will be summarized with descriptive statistics, including mean, median, and SD for continuous variables (eg, age) and proportions for categorical variables (eg, sex). In regression models, all coefficients will be estimated with 95% CIs, and for the point estimates, 2-sided *P* values will be used. All analyses will be conducted as intent-to-treat using all available data for participants who receive the intervention. We will do multiple imputation using within-subject data during the intervention as a sensitivity analysis to handle missing data. For analyses of the primary outcome, missing step data will be assessed conservatively and will be marked as having the absence of the target behavior (eg, walking 250 steps each h during their preidentified, preferred 4-h period each day for 7 consecutive d) for that day or days.

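### The stated 92% power is for 60 participants left after dropout and a 1-sided test, but the planned primary analysis keeps about 80, scores missing days as failure and tests 2-sided

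*Protocol article*

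**What the plan says.** Sample Size Calculation: the plan starts from 100 enrolled caregivers. On losses before the intervention it states "Up to 20% attrition is expected following the 2-week baseline period" (20 participants), and a further 25% (20 of the remaining 80) are expected to be lost to follow-up, to withdrawal or for other reasons around the 10-week intervention. The section then concludes "The trial still will have a sufficient sample (n=60) to provide adequate power". The power sentence begins "Assuming a null habit formation rate of 30% with a sample size of n=60", uses a 1-sided binomial test at 5%, and gives about 92% power "if the true habit formation rate is at 50% or above".

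General Statistical Analytical Approach: "All analyses will be conducted as intent-to-treat using all available data for participants who receive the intervention". For the primary outcome, "missing step data will be assessed conservatively and will be marked as having the absence of the target behavior" for the day or days concerned.

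Primary Outcome and Analysis: success is any run of 7 consecutive qualifying days in the 70-day intervention. The observed proportion is compared with 30% by a one-sample binomial test at a 2-sided 5% level.

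**The concern.** The two parts of the article treat attrition in different ways. The power calculation takes the 20 intervention-period losses out of the sample and leaves the success rate at 50%. The analysis rules leave those 20 in the denominator. A participant who stops supplying step data without an earlier 7-day run then counts as not having formed a habit. Attrition so handled pulls the tested proportion toward the 30% null, which the power calculation does not reflect. The sidedness of the test also differs between the two sections.

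This is the only power statement for the primary hypothesis of a single-arm trial. If it does not describe the planned test, a non-significant result could be read as failure of the intervention in a well-powered trial when the power was in fact unknown or lower.

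**Working it through.** **Inputs from the article.** Enrolled 100; lost at baseline 20; treated 100 − 20 = 80; lost during the intervention 25% × 80 = 20; remaining 60. Null rate 30%, alternative 50%. The power statement uses a 1-sided 5% test; the planned test is 2-sided 5%.

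**Input not in the article.** The habit rate q among the 20 dropouts. It is an assumption here, varied from 0% to 50%.

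**Step 1: reproduce the stated figure.** Find the smallest r with P(Bin(60, 0.30) ≥ r) ≤ 0.05. This is r = 25 (tail 0.0362). Power = P(Bin(60, 0.50) ≥ 25) = 0.9225, so the 92% is arithmetically correct for n=60, 1-sided.

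**Step 2: change only the sidedness.** At n=60 with an upper tail of at most 0.025, r = 26 (tail 0.0196), and power at 50% is 0.8775.

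**Step 3: the planned test on the planned set.** At n=80 with an upper tail of at most 0.025, r = 33 (tail 0.0211). With the 1-sided 5% test, r = 32 (tail 0.0360).

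**Step 4: the 50% read as the rate among all treated.** P(Bin(80, 0.50) ≥ 33) = 0.954. The 1-sided test gives 0.972.

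**Step 5: the 50% read as the rate among the 60 completers.** Overall rate = (60 × 0.50 + 20 × q)/80. Power = P(Bin(60, 0.50) + Bin(20, q) ≥ r).

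| Dropout habit rate q | Overall rate | Power, 2-sided (r=33) | Power, 1-sided (r=32) |
|---|---|---|---|
| 0% | 37.5% | 0.26 | 0.35 |
| 10% | 40.0% | 0.45 | 0.55 |
| 20% | 42.5% | 0.64 | 0.72 |
| 30% | 45.0% | 0.79 | 0.85 |
| 40% | 47.5% | 0.89 | 0.93 |
| 50% | 50.0% | 0.95 | 0.97 |

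In the bottom-case row, 9 points of the fall (35% to 26%) come from the change of sidedness alone. Under the 2-sided test, power is about 50% when q is about 12.5%.

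**Step 6: power by overall rate, for the restated text.** Treating all 80 as binomial at the overall rate, 2-sided test: 0.28 at 37.5%, 0.73 at 44%, 0.95 at 50%. (At 37.5% this is 0.28 instead of 0.26 because the split into 60 completers and 20 certain failures is no longer fixed.) If every dropout fails, the completer rate implied is overall rate × 80/60: 37.5% gives 50%, 44% gives 58.7% (about 59%), and 50% gives 66.7% (about 67%).

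**The case against.** The strongest reply is that the article never says the 50% belongs to completers. The Objective in the Abstract sets the target among caregivers receiving the intervention, which is the analysis population. On that reading power is about 95%, above the stated 92%, and n=60 was merely cautious. This stands as a possible reading. It does not rescue the power statement, which ties the 50% to n=60 and so leaves the population open. That reading also implies that up to 67% of completers form the habit, which the article does not state.

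Second, attrition is not the same as missing step data. Trial completion is defined by submitting the end-of-study surveys. Partial withdrawers may go on supplying Fitbit data, and participants may pause and resume. Missing data are scored by day, so someone who completed a 7-day run before leaving still counts as a success. All of this stands, and it is why 26% is a floor.

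A reader might infer from the 26% that an intervention working in half of completers would probably be declared ineffective. The article does not support that. It would require both the completer reading of the 50% and a dropout habit rate below about 12.5%, and the article gives neither.

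**Conclusion.** The inconsistency is real, and nothing in the article reconciles it. The 92% is computed correctly, but for a 60-person, 1-sided analysis. The plan describes an analysis of about 80 people, 2-sided, with missing days scored as failure.

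The direction and size of the discrepancy are not settled by the article. Power is about 95% if the 50% refers to all treated participants. If it refers to completers, power ranges from 26% (no dropout ever forms a habit) to 95% (dropouts do as well as completers). These figures assume exactly 80 treated and 60 completers, independent outcomes and the exact binomial test. The fault lies in the power statement; the intent-to-treat and missing-as-failure rules are not in question.

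**What to change.** Keep the intent-to-treat set and the rule that scores missing days as failure. Replace the n=60, 92% statement with power for about 80 treated participants under the planned 2-sided 5% test. Define the habit rate explicitly over all treated participants, with missing scored as failure. Give power at overall rates of 37.5%, 44% and 50% (about 28%, 73% and 95%), with the completer rate each implies if all dropouts fail (50%, 59% and 67%).

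This changes only wording in the sample-size section and, for consistency, in the SAP. No extra enrolment is needed. The cost is that the stated power may look less favourable.

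### The 92% power belongs to a one-sided 5% test, but the primary analysis is a two-sided 5% test, whose power at n=60 is about 88%

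*Protocol article*

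**What the plan says.** The Primary Outcome and Analysis section sets the benchmark ("We will use a null hypothesis rate of 30" per cent) and the test: the observed proportion forming a habit is compared with that null "using a 1-sample binomial test with a 2-sided α at 5" per cent. The observed proportion is also to be reported with a 95% confidence interval.

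The Sample Size Calculation section uses the same null and 60 participants ("Assuming a null habit formation rate of 30% with a sample size of n=60"). It then states that "a 1-sided, one-sample binomial test at 5% significance will have about 92% power to declare the BCT intervention effective"; the alternative behind this figure is a true rate of at least 50%.

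The General Statistical Analytical Approach section says "2-sided *P* values will be used", but that sentence concerns regression coefficients. It does not settle which sidedness governs the binomial test.

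**The concern.** The two sections describe the same endpoint, null and family of test, and differ only in sidedness. A two-sided 5% test allows about 2.5% in the direction of benefit, so its bar is higher than that of a one-sided 5% test. Two things follow.

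- The stated power is not the power of the planned primary analysis.
- The sample size section speaks of declaring the intervention effective, so a reader can find two success thresholds in one document. A result on the boundary could be called positive or negative depending on which section is followed.

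This is the primary hypothesis test of a single-arm trial that is already enrolling and is meant to inform Stage III studies. Sidedness chosen after the data are seen would be open to challenge.

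**Working it through.** **Inputs**
- Null rate p0 = 0.30 (Primary Outcome and Analysis; Sample Size Calculation).
- True rate under the alternative p1 = 0.50, and n = 60 (Sample Size Calculation).
- Alpha 5%: two-sided in Primary Outcome and Analysis, one-sided in Sample Size Calculation.

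**Formula.** Let X be the number of participants who form a habit, X ~ Bin(60, p). For a critical count r, the upper-tail error is P(X ≥ r | 0.30) and the power is P(X ≥ r | 0.50).

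| r | r/60 | P(X ≥ r given 0.30) | exact two-sided p | P(X ≥ r given 0.50) |
|---|---|---|---|---|
| 24 | 40.0% | 0.0632 | 0.0927 | 0.9538 |
| 25 | 41.7% | 0.0362 | 0.0657 | 0.9225 |
| 26 | 43.3% | 0.0196 | 0.0335 | 0.8775 |

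**Step 1: reproduce the stated figure.** For the one-sided 5% test, the smallest r with upper tail at or below 0.05 is 25 (0.0362; r = 24 gives 0.0632). Power is 0.9225, or 92.2%. This matches the stated figure, so the one-sided test is what was calculated.

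**Step 2: the test in the analysis section.** For the two-sided 5% test, r = 25 fails: its upper tail of 0.0362 exceeds 0.025, and the exact two-sided p is 0.066 (minimum-likelihood method) or 0.072 (doubling the tail). At r = 26 the upper tail is 0.0196 and the two-sided p is 0.033 or 0.039. The boundary is therefore 26, and power is 0.8775, or 87.7%.

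**Step 3: the size of the gap.**
- Power: 0.9225 − 0.8775 = 0.0450, or 4.5 percentage points. This is the chance of landing on exactly 25 of 60 when the true rate is 50%.
- Type II error: 1 − 0.9225 = 7.8% becomes 1 − 0.8775 = 12.3%.

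**Step 4: the boundary result.** At 25 of 60 the one-sided rule rejects (p = 0.036) and the exact two-sided rule does not (p = 0.066). The exact 95% confidence interval is 29.1% to 55.1%, which contains 30%. A one-sided success would thus sit beside an exact interval that includes the null.

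**Step 5: could an approximation rescue the 92%?** Normal-approximation power is as follows.

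| Variant | One-sided 5% | Two-sided 5% |
|---|---|---|
| Null and alternative variances | 94.4% | 90.4% |
| Same, continuity-corrected | 92.8% | 88.0% |
| Alternative variance only | 92.7% | 87.3% |

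No two-sided variant reaches 92%.

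**Step 6: a larger denominator.** The article analyses everyone who receives the intervention, about 100 − 20 = 80 on its own attrition figures. At n = 80 the exact critical counts are 32 (one-sided, upper tail 0.0360) and 33 (two-sided, upper tail 0.0211, two-sided p 0.037). The rules still differ by one count.

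**The case against.** - **Nothing is miscalculated.** The 92% is right for the test it names. That stands: the fault is an inconsistency between two sections, not an arithmetic slip.
- **The consequence is small.** Power of about 88% is above the customary 80%, and the section's conclusion that 60 participants are adequate survives. That also stands. The reason to act is the conflicting rule for the primary test more than the lost power.
- **There is really only one decision rule.** The sample size section is a planning calculation, and only the analysis section says how the observed proportion will be tested. This has force, and it is why the two-sided test should be the one kept. But the planning text describes its test as the one that declares the intervention effective, and nothing ranks one section over the other.
- **The clash at 25 of 60 depends on the exact test and on exactly 60 being analysed.** True. The article does not use the word exact. An uncorrected z-test at 25/60 gives z = (0.4167 − 0.30)/√(0.21/60) = 1.97, two-sided p about 0.049, and would reject. With continuity correction z = 1.83 and it would not. The exact reading is the natural one, because the test is called binomial and the exact calculation gives the stated 92%. At n = 80 the clash moves to 32 rather than disappearing.
- **An unseen analysis plan may settle it.** It might, but it would not correct two conflicting statements in the published article.

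**Conclusion.** The concern holds. The article powers a one-sided 5% test and plans a two-sided 5% test of the same hypothesis. Under the planned test, power at n = 60 is 87.7% rather than 92%, and success requires 26 rather than 25 of 60. These figures assume the exact binomial test, a true rate of 50% and 60 participants analysed. The mismatch in sidedness depends on none of these. The sample size need not change on this ground.

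**What to change.** - In Sample Size Calculation, delete the one-sided wording and name the two-sided 5% exact binomial test already set for the primary analysis.
- Restate the power as about 88% for n = 60 with a null of 30% and a true rate of 50%, and give the critical count (26 of 60).
- Add the word exact to the test in Primary Outcome and Analysis, which removes the dependence on the choice of approximation.
- Because the analysis set is everyone who receives the intervention, also give the figures for n = 80: critical count 33, power 95.4% if the true rate among all 80 is 50%. Missing step data count as absence of the behavior, so dropout could pull that rate below 50%. State the rate assumed.

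The cost is one sentence on sidedness and power, a few words for the other items, and a slightly less favourable power figure. No change to enrollment, null rate or primary test is needed. It should be settled before outcome data are analysed.
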